#### General psychological measures

With the *SF-1* single item measure for self-reported health status (SRHS [39];), included in the SF-36 [40], participants are asked the question: “In general, would you say your health is?” with the response options 1 = “poor”, 2 = “fair”, 3 = “good”, 4 = “very good”, and 5 = “excellent”.

With the *EUROHIS-QoL Index* [5] general quality of life is assessed with a reliability score of α = .85. Different response options are given, depending on the question (e.g., “How would you describe your quality of life?”).

With the *Self-Construal Scale* [62] four context-relevant self-construals are assessed (Making decisions, Looking after oneself, Communicating with others, Dealing with conflicting interests) with reliability scores between α = .74–.87. Participants are asked how well a statement describes them (e.g., “Usually I follow the advice of others when making important decisions”) on a 5-point Likert scale from 1 = “doesn’t describe me at all” to 5 = “describes me very well”.

With the German version of the *MacArthur Scale* [22] the subjective socio-economic status is assessed. The participants are asked to define their status on a scale from 1 = “lowest status” to 10 = “highest status” after being asked to imagine that all people in Germany are somewhere on a “social ladder”, the people at the top having the highest income, best education, and best jobs.

#### Intermediary process measures

With a new scale, taken and adapted from different measurements (considering the meta-analysis of [42]) continuum belief of mental illness is assessed. Participants are asked whether they agree with the statements (e.g., “Now and again most of us have symptoms of a mental illness”) on a 5-point Likert scale from 1 = “don’t agree at all” to 5 = “I agree completely”. Final reliability scores will be calculated with the data. This instrument will be used to test the hypothesis H4.

With a short form of the *Depression Literacy Scale* [20] depression literacy is assessed. Participants are asked whether a statement (e.g., “Too little or too much sleep can be a sign of depression”) is 1 = “true”, 2 = “false”, or 3 = “don’t know”. Based on secondary data analysis, the reliability score for the short-form is α = .72. This instrument will be used to test the hypothesis H5.

With a list of possible causes [51] causal belief is assessed. Participants are asked whether they believe a listed cause (e.g., “Living in a big city”) is a cause for their complaints on a 5-point Likert scale from 1 = “definitely is not a cause” to 5 = “definitely is a cause”. This instrument will be used to test the hypotheses H1 and H6.

Self-efficacy is assessed with context-relevant adaptations of items taken from the BRAHMS-Study [43] and a study assessing the health care use of homeless people [23]. Concerning self-efficacy for self-help, participants are asked to rate how certain they are that they can overcome specific barriers (e.g., “… if my complaints don’t get better despite my efforts”) on a 5-point Likert scale from 1 = “very uncertain” to 5 = “very certain”. Concerning self-efficacy for seeking professional help, participants are asked to rate how confidant they are that they can overcome barriers of the health care system (e.g., “I am able to deal with long waiting times”) on a 5-point Likert scale from 1 = “not confident” to 5 = “very confident”. Final reliability scores for both of these adapted instruments will be calculated with the data. These instruments will be used to test the hypotheses H2 and H3.

#### Help seeking measures

With the *B-IPQ-R* [8] the subjective sense of illness is assessed. All of the items except the causal question are rated using a 0 to 10 response scale. Five of the items assess cognitive illness representations: consequences (item 1), timeline (item 2), personal control (item 3), treatment control (item 4), and identity (item 5). Two of the items assess emotional representations: concern (item 6) and emotions (item 8). One item assesses illness comprehensibility (item 7). Assessment of the causal representation is by an open-ended response item adapted from the IPQ-R, which asks patients to list the three most important causal factors in their illness (item 9). Test-Retest reliability after 6 weeks lies between .42 (personal control) and .75 (identity).

With the *SELF-I* [48, 52] the self-identification as mentally ill is assessed. Participants are asked to appraise their current problems (e.g., “My present problems could be the first signs of a mental disorder”) on a 5-point Likert scale from 1 = “don’t agree at all” to 5 = “agree completely”. The scale has excellent internal reliability (α = .90). This instrument will be used to test the hypotheses H4, H5, H6, and H7.

With the *ATSPPH-SF* [18] attitudes towards help-seeking is assessed. Participants are asked to rate how much they agree with certain statements regarding seeking help from a psychiatric or mental health professionals (e.g., “Emotional difficulties like many things, tend to work out by themselves”) on a 4-point Likert scale from 1 = “strongly disagree” to 4 = “strongly agree”. Internal reliability is very good (α = .84).

With an adapted version of the *ACMQ* [27] the motivation of subsequent help-seeking is assessed. Participants are asked to rate how much they agree with statements of why they might seek out help (e.g., “I could imagine seeking help for my current complaints, because I feel like I would personally benefit from it”) on a 5-point Likert scale from 1 = “strongly disagree” to 5 = “strongly agree”. Final reliability scores will be calculated with the data.

With a list of potential persons (e.g., psychotherapist) and institutions (e.g., counselling centre) where participants could seek help (adapted from [41]) help-seeking intention and behaviour is assessed on a 7-point Likert scale from 1 = “extremely unlikely” to 7 = “extremely likely”. This response format has previously been validated for general help-seeking [64]. This instrument will be used to test the hypotheses H1, H2, and H3.

With the *TPB* [60, 61] subjective norms (items 1 to 4), attitudes (items 5 to 7) and perceived control (items 8 to 10) of help-seeking, theoretically based on the Theory of Planned Behaviour [1], is assessed. All items measuring subjective norms (α = .84) and perceived behavioural control (α = .74) were rated on a 7-point Likert scale from 1 = “strongly disagree” to 7 = “strongly agree”. To measure attitudes (α = .69), participants indicated their attitude towards seeking professional help on three pairs of bipolar items (e.g., “good” – “bad”).

#### Stigmatising attitudes

Different instruments are used to assess a scope of stigmatising attitudes that theoretically influence the help-seeking process. These instruments and questions will be used to test the hypotheses H4, H5, H6, and H7.

With the *SSMIS-public* and *-self-SF* [12] perceived public stigma and the agreement thereof are assessed. Participants are asked to rate how much they agree with statements concerning people with a mental illness (e.g., “Most people with mental illness are dangerous”). The statements are primed with “I think the public believes …” (public-stigma) or “I think …” (self-stigma) and participants can rate their answers on a 5-point Likert scale from 1 = “strongly disagree” to 5 = “strongly agree”. Internal reliability for the public-stigma subscale (α = .73) and self-stigma subscale (α = .75) are very good.

With the *SDS* [2] the tendency of a person to distance themselves socially from people suffering from mental illnesses is assessed. Participants are asked to rate how much they agree with statements concerning people with a mental illness (e.g., “How willing would you be about renting a room in your home to a person with severe mental illness?”) on a 5-point Likert scale from 1 = “very unlikely” to 5 = “very likely”. Internal reliability is very good (α = .85).

With four items the agreement with the stereotype of blame is assessed [49]. Participants are asked to rate how much they agree with statements (e.g., “Persons with mental illness are to blame for their problems”) on a 5-point Likert scale from “1 = don’t agree at all” and “5 = agree completely”. Internal reliability is very good (α = .79).

With three items support for discrimination of people with a mental illness is assessed [49]. Participants are asked to rate how much they agree with statements (e.g., “If persons with mental illness do not consent to medical treatment, they should receive compulsory treatment”) on a 5-point Likert scale from 1 = “don’t agree at all” to 5 = “agree completely”. Internal reliability is good (α = .71).

With the *SSOSH-SF* [7] the proclivity of self-stigma for seeking out professional help for one’s mental health problems is assessed. Participants are asked to rate how much they agree with statements (e.g., “I would feel inadequate if I went to a therapist for psychological help”) on a 5-point Likert scale from 1 = “don’t agree at all” to 5 = “agree completely”. Internal reliability is excellent (α = .87).

With the *ERMIS* [4] the emotional reaction towards a person with a mental illness is assessed, with its subscales indicating pro-social reactions (e.g., “I feel pity towards the person”), fear (e.g., “The person makes me feel afraid”), and anger (e.g., “I react annoyed”) towards a person with a mental illness. Participants are asked to rate how much they agree with statements on a 5-point Likert scale from 1 = “don’t agree at all” to 5 = “agree completely”. Final reliability scores will be calculated with the data.

With two items shame experienced for being mentally ill (“Would you feel shame, if you had mental problems?”) and seeking out help (“Would you feel shame, if others knew that you were seeking out professional help for you mental problems?”) is assessed. Participants can rate their response with the options 1 = “not at all”, 2 = “a little”, 3 = “fairly”, 4 = “fairly strong”, and 5 = “very strong”. Final reliability scores will be calculated with the data.

#### Context assessment measures

With the *PHQ-9* [32] depressive symptoms are assessed. Participants are asked to rate how often they have been bothered by problems over the last 2 weeks (e.g., “Little interest or pleasure in doing things”) with the response options 1 = “not at all”, 2 = “several days”, 3 = “more than half the days”, 4 = “nearly every day”. Internal reliability (α = .89) and test-retest reliability after 48 h (*r* = .84) are excellent.

With the *GAD-7* [32] anxiety is assessed, seen as anxiety disorders are often co-morbid with depressive disorders. Participants are asked to rate how often they have been bothered by problems over the last 2 weeks (e.g., “Feeling anxious, nervous, or on edge”) with the response options 1 = “not at all”, 2 = “several days”, 3 = “more than half the days”, 4 = “nearly every day”. Internal reliability (α = .92) and test-retest reliability (*r* = .83) are excellent. Additionally, the open-ended question “Do you have further psychological complaints?” is asked, to control for other co-morbid symptoms.

With five consecutive questions [61] perceptions about context and infrastructure of help-seeking are assessed: (i) local service awareness: whether they knew where to find a professional in the vicinity (1 = “yes”, 2 = “no”), (ii) spatial distance: if so, how long it would take them to reach the professional (in minutes), (iii) accessibility: whether they believed they would get an appointment (1 = “yes”, 2 = “no”), and if so, (iv) temporal distance: when this appointment would take place (1 = “today”, 2 = “tomorrow”, 3 = “in ‘xx’ days”, 4 = “in ‘xx’ weeks”, 5 = “in ‘xx’ months”, with the option to enumerate “xx days/weeks/months,” (v) treatment efficacy beliefs: to what extent they consider it likely that they get appropriate help there for their current problems from 1 = “very unlikely” to 7 = “very likely”.

With three to seven questions (filtered, depending on previous answers) previous treatment experience (e.g., “Have you ever received treatment for mental illness in your life?”) and official diagnosis (“What official diagnosis did the doctor give you?”) are assessed. Additionally, treatment contentment was assessed with the question “How content were you with your psychiatric or psychotherapeutic treatment in general?” to which the participants can respond on a 5-point Likert scale from 1 = “very discontent” to 5 = “content”. These questions will be used to test the hypotheses H3 and H7.

Finally, questions were formulated to assess the adherence to (“To what extent do you adhere to the measures to contain the coronavirus?”), felt restriction of (“How much do you feel restricted by the measures?”), and felt mental burden of the lockdown restrictions (“How much psychological strain do the measures put on you?”) with respective 5-point Likert response scales. The perceived possibility to go to a general practitioner or therapist is assessed: “Despite the current corona pandemic, would you go to the doctor or therapist because of your psychological complaints?” and participants can respond 1 = “Yes, I would go anyway”, 2 = “No, I wouldn’t go at the moment because of Corona”, and 3 = “No, I wouldn’t go anyway”.

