**Methods:**

A quasi-experimental online study will be carried out to assess the effect of different intervention variables relevant for the help-seeking process. The study is conceived as a fractional factorial design. Participants will be screened for depressive complaints (PHQ-9 sum score ≥ 8) and current psychiatric/psychotherapeutic treatment. After baseline assessment the participants will be randomly allocated into one of the 24 study groups receiving different combinations of the vignette-based intervention aiming to reduce stigma and support help-seeking. Next, relevant outcome measures will be administered a second time. In a 3- and 6-month follow-up help-seeking behaviour will be measured. Gamified elements and avatar-choice techniques will be used to heighten study immersion and adherence.

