#### Inclusion criteria

Participants will be included if they are 18 years and older and score ≥ 8 on the PHQ-9, indicating at least mild depressive complaints [31]. This cut-off score was decided upon after extensive research on the use of the PHQ in comparable research [30, 37]. The participants have to be able to read and comprehend German.

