#### Exclusion criteria

Participants will be excluded if they are currently receiving psychiatric or psychotherapeutic treatment. There are no further exclusion criteria.

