### Outcome measures

Table 2 shows the variables that will be investigated at different times during the study and the instruments used to assess these. They have been classified into general psychological, intermediary process, help-seeking, stigmatisation, and context assessment measures. The final selection of the instruments, some adapted to fit the current research setting, were based on theoretical research and pre-study test results (*N* = 227), in which psychometric properties, especially of the adapted instruments, were analysed.

**Table 2 Tab2:** Questionnaires employed at the different study assessment times

Study assessments & measures	Number of items	Study time points			
		T0	T1	T2	T3
Socio-demographic					
Gender	1	X			
Month& year of birth	2	X			
Family status & partner	3	X			
Education	2	X			
Employment	2	X			
Income	1	X			
General psychological					
Subjective general health (SF-1)	1	X		X	X
Quality of life (EUROHIS-QoL Index)	8		X	X	X
Self-construal Scale (SCS)	24	X			
Subjective Socio-Economic Status	1				X
Intermediary process					
Continuum beliefs (CB_new)	12	X	X	X	X
Causal beliefs (List)	18	X	X	X	X
Mental health literacy, depression specific (D-Lit)	12	X	X	X	X
Self-efficacy to help oneself	6	X	X	X	X
Self-efficacy to seek out professional help	7	X	X	X	X
Help-seeking					
Subjective sense of illness (B-IPQ-R)	9	X		X	X
Self-identification as mentally ill (SELF-I)	5	X	X	X	X
Attitudes towards help-seeking (ATSPPH-SF)	10	X	X	X	X
Motivation behind help-seeking (ACMQ)	6	X	X		
Help-seeking intention (List)	16	X	X	X	X
Help-seeking subjective norms, attitudes and perceived control (TPB)	10	X	X	X	X
Help-seeking behaviour/ health-care utilisation	18			X	X
Stigmatisation					
Perceived public stigma and the agreement with stigma (SSMIS-public & -self-SF)	10	X	X	X	X
Social distance stigma (SDS)	7	X	X	X	X
Discrimination of mental illness	3	X	X	X	X
Sense of blame for mental illness	4	X	X	X	X
Self-stigma for seeking out professional help (SSOSH-SF)	3	X	X	X	X
Shame for being mentally ill and seeking out help	2	X	X	X	X
Emotional reaction towards a person with mental illness (ERMIS)	10	X	X	X	X
Context					
Depressive Symptoms (PHQ-9)	9	X	X	X	X
Anxiety Symptoms (PHQ-anxiety module)	7		X		
Differential diagnosis	1		X		
Previous treatment experience	3–7		X		
Perceived availability and accessibility to the health care system	1–5		X		
Covid-19 questions	4	X		X	X
	∑ = 246				

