### Limitations and generalisability

Our study design has a few limitations. Firstly, since one of the aims of the study is to find points of interests for evidence-based design and evaluation of online offers, the setting has to be online. Online studies have the problem of non-accountability. The attention of the participants is not controlled for, they can take unnecessary and lengthy breaks and it is not possible to track what they might do while participating, impeding data quality. Inherent to an online setting, the anticipated drop-out rate is substantial between the first baseline-assessment and the follow-up assessments and it is difficult to ensure study adherence over such a long period of time. This said, the online setting can be considered a strength since the targeted group is people with depression, who might be more willing to participate in a low-threshold online study than a full clinical trial. Secondly, the intervention is short and informational, without sufficient material to reflect upon one’s own problems extensively. The intervention, furthermore, is administered only once. Both these limitations will probably mean small effect sizes. Thirdly, only self-report measures can be used, which are inherently subjective and prone to perception biases. Considering the difficult subject matter social desirability might be an issue though online-anonymity should counteract this bias. Fourthly, the participants will have to be able to access electronic devices, wherefore there will most likely be a bias in our study population of people who are more technically proficient than others (especially in the age group 65+). Even though these limitations mean a reduced internal validity they reflect the real-life, online setting, therefore, external validity of the study will be high. A further limitation is the recruitment method. Participants will be recruited through an online-panel. Consequently, they have had to have signed-up previously and probably are part of a highly motivated sub-population, even though they all have a PHQ-9 score of at least eight indicating mild depression or higher. They are also used to answering questionnaires quickly, which might reduce data quality, since they will be aware of questionnaire internal attention checks.

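### On the printed 1 to 4 item codes, the lowest possible PHQ-9 sum is 9, so the entry rule of 8 or more excludes nobody; coding and cut-off must be put on one scale

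*Protocol article*

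**What the plan says.** The section on context assessment measures describes the PHQ-9 with "response options 1 = “not at all”, 2 = “several days”, 3 = “more than half the days”, 4 = “nearly every day". It gives no other scoring instruction for the scale. Table 2 lists the PHQ-9 with nine items, administered at T0, T1, T2 and T3.

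The abstract's methods paragraph makes the scale a screening instrument ("Participants will be screened for depressive complaints") and states the rule as "PHQ-9 sum score ≥ 8", so the item values are added. The inclusion criteria repeat the threshold and interpret it: "score ≥ 8 on the PHQ-9, indicating at least mild depressive complaints". The limitations section relies on it again, saying of the participants that "they all have a PHQ-9 score of at least eight indicating mild depression or higher".

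The remaining entry rules are age 18 or over, the ability to read and understand German, and no current treatment: "Participants will be excluded if they are currently receiving psychiatric or psychotherapeutic treatment. There are no further exclusion criteria".

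**The concern.** A cut-off selects only if some attainable scores fall below it. Read together, the printed item codes and the printed threshold leave no such score. The article nevertheless treats the threshold as selective and says what passing it means.

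The PHQ-9 rule is the only entry rule that ties the sample to depressive complaints. The others concern age, language and current care. The study asks about help-seeking for one's own complaints, about their perceived causes, and about self-identification as mentally ill. These questions presuppose that complaints exist. If the filter added the codes exactly as printed, the symptom screen on a general online panel would do nothing. Someone who wishes to replicate the screen, or to use the shared data, also cannot tell from the article which scale the 8 belongs to.

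**Working it through.** **Inputs**
- Lowest and highest printed item code: 1 and 4 (Context assessment measures).
- Number of items: 9 (Table 2).
- Scoring operation and threshold: sum, at least 8 (Abstract, Methods; threshold repeated under Inclusion criteria and Limitations).

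**Step 1: range of the sum on the printed codes**
- Minimum = 9 × 1 = 9.
- Maximum = 9 × 4 = 36.

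**Step 2: who fails the rule**
- There are 4^9 = 262,144 possible response patterns.
- A pattern fails if its sum is below 8. Since the minimum is 9, the number that fail is 0.
- A respondent who answers 'not at all' nine times scores 9 and passes.

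The plan's statement that a score of 8 or more marks at least mild complaints is therefore not reproduced on the printed codes.

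**Step 3: size of the mismatch under one alternative**

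The article does not state a 0 to 3 scoring. It is used here only as an assumption, to show scale.
- Range = 9 × 0 = 0 to 9 × 3 = 27.
- Patterns with a sum of 7 or less: C(16, 9) − 9 × C(12, 9) = 11,440 − 9 × 220 = 11,440 − 1,980 = 9,460. Direct enumeration gives the same count.
- So 9,460 of 262,144 patterns fail, including the one with no symptoms, and the rule screens.
- Each item differs by 1 between the two codings, so the sums differ by 9, and 8 on this scale equals 8 + 9 = 17 on the printed codes.

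Counts of patterns are not proportions of people. They show only whether the rule can exclude anyone.

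**Step 4: what is not affected**
- The sample size. With f = 0.10, 24 groups, α = 0.05, two measurements and an assumed correlation of 0.5, N = 840 gives power 0.9545 against the stated 0.95. No PHQ-9 quantity enters that calculation.
- The self-harm notice described under Harms. It is triggered by the answer label, not by a number.
- The GAD-7. It is printed with the same 1 to 4 codes, but no entry rule uses it.

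**The case against.** The best defence is that the digits are answer labels and not scoring weights. The article numbers options from 1 in places where the digits cannot sensibly be added. The depression literacy items are coded 1 for true, 2 for false and 3 for don't know, and the service awareness and accessibility questions are coded 1 for yes and 2 for no. On this view the PHQ-9 digits are platform codes that are rescored before summing, and the article left the scoring syntax to the full protocol. The intended population is also clear, because three places use 8 as a selective cut-off. The soft launch of N = 100 and the plausibility checks could reveal a filter that rejects nobody.

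Much of this stands. It makes a harmless explanation quite possible. It does not remove the contradiction. The article prints one coding and one sum threshold, the two do not fit, and no rescoring is stated anywhere. The soft launch is described as a check of data quality and technical functioning, with no mention of testing the entry filter.

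A reader might go further and infer three things that the documents do not support:
- **That the trial enrols everyone, mostly people with no need for help, and that every effect is diluted.** The filter itself is not shown, the article gives no PHQ-9 distribution for the panel, and the other entry rules still exclude people.
- **That the severity analyses are spoiled by a 9-point shift.** Adding a constant leaves correlations, regression slopes for severity and standardised path coefficients unchanged. Only raw levels and absolute cut-offs move.
- **That 0 to 3 scoring, or a cut-off of 17, is the documented intention.** Neither appears in the article.

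**Conclusion.** The point holds as an internal contradiction in a rule that determines who enters the trial. On the printed codes the threshold lies one point below the scale minimum, and the PHQ-9 rule excludes 0 of 262,144 possible response patterns. The arithmetic is exact and rests only on nine items, codes of 1 to 4, and simple summation.

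What it means for the data is open. If the codes were rescored before summing, the fault is one of reporting. If they were summed as printed, the symptom screen was inactive. The article does not let a reader decide between the two. The contradiction should be resolved because the symptom criterion depends on it, not because enrolment of symptom-free people has been shown.

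**What to change.** - **Text.** Reconcile the abstract's methods paragraph, the inclusion criteria, the PHQ-9 description and the limitations section. State the item values used to form the sum, for screening and for analysis, so that the coding and the cut-off are on the same scale. Which of the two needs changing is for the investigators to establish from the filter that was actually programmed. Add the same scoring statement for the GAD-7.
- **Check.** Confirm, in the soft-launch or screening data or by a test entry in the survey platform, that a respondent who answers 'not at all' to all nine items is screened out. The article gives January/February 2021 as the first recruitment time and was published in November 2021, so such data may already exist.
- **If raw printed codes were summed.** Re-derive each participant's eligibility from the PHQ-9 item responses collected at T0, and report how many enrolled participants do not meet the intended criterion.

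The cost is a sentence or two of protocol text and one check of the filter. The re-derivation needs no new data collection.
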